## Abstract

**Background:**

Autism spectrum disorder (ASD) is a neurodevelopmental condition affecting 0.7% of children globally, with 90% experiencing comorbid gastrointestinal (GI) symptoms. Fecal microbiota transplantation (FMT) may modulate ASD symptoms via the microbiota-gut-brain axis (MGBA).

**Methods:**

This open-label single-arm trial enrolls 30 children (2–12 years) with moderate-to-severe ASD, defined as a Childhood Autism Rating Scale (CARS) score of ≥36. Participants receive 3 nasojejunal FMTs (5 mL/kg) over 5 days. The primary outcomes are GI symptom improvement, assessed using the Gastrointestinal Symptom Rating Scale (GSRS), and ASD severity, assessed using the CARS. Secondary outcomes include social responsiveness (Social Responsiveness Scale, SRS), aberrant behaviors (Aberrant Behavior Checklist, ABC), and gut microbiota changes assessed by metagenomic next-generation sequencing (mNGS).

**Ethics and dissemination:**

Ethical approval obtained from Shenzhen Children's Hospital Ethics Committee. Results will be disseminated via peer-reviewed publications and conference presentations.

**Clinical Trial Registration**: https://www.chictr.org.cn/showproj.html?proj=229136, identifier ChiCTR2400083998. Registered on 2024-05-08. Registered title: “Efficacy and safety of fecal microbiota transplantation in treatment of autism spectrum disorder: a prospective single-center intervention study”.

## Introduction

1

Autism Spectrum Disorder (ASD) is a complex neurodevelopmental disorder characterized by core features of social communication deficits, restricted interests, and repetitive behaviors, often accompanied by metabolic dysregulation, immune dysfunction, and gastrointestinal (GI) symptoms (1). The global prevalence of ASD is approximately 0.6%, with a significant upward trend, making it a critical public health concern in pediatric mental health (2).While the exact etiology of ASD remains incompletely understood, the interplay between genetic and environmental factors is recognized as the primary pathogenic mechanism (1, 3). In recent years, gut microbiota dysbiosis and its impact on neurodevelopment via the “Microbiota-Gut-Brain Axis” (MGBA) have emerged as a research focus (4).Fecal Microbiota Transplantation (FMT), an innovative therapy to modulate gut microbiota, offers a novel direction for ASD treatment (5, 6).

In addition to core behavioral manifestations, approximately 90% of children with ASD experience comorbid GI symptoms such as bloating, abdominal pain, constipation, or diarrhea, which are positively correlated with ASD severity (7). Epidemiological data indicate a marked increase in ASD prevalence over the past decade. For instance, the prevalence among 8-year-old children in the United States rose from 1.1% in 2008 to 2.3% in 2018 (8). In China, the first multicenter, large-scale epidemiological study reported a prevalence of 0.7% in children aged 6–12 years, with a male-to-female ratio of approximately 4:1 (9). Although genetic factors dominate ASD pathogenesis (1), environmental contributors such as perinatal infections and antibiotic exposure also play critical synergistic roles (10). Current clinical management of ASD primarily relies on behavioral interventions (e.g., Applied Behavior Analysis) and pharmacotherapy (e.g., risperidone, aripiprazole). However, the efficacy of behavioral therapies requires further validation (11), while medications are limited by adverse effects such as extrapyramidal symptoms and metabolic disturbances (12). Consequently, the exploration of safe and effective therapeutic strategies remains urgent.

The gut microbiota, also termed gut microbiota, constitutes a complex ecosystem comprising bacteria, viruses, fungi, and protozoa, predominantly residing in the colon. Bacteria account for over 99% of this ecosystem, with approximately 40 trillion bacterial cells and more than 1,000 species in the human gut. The diversity and functional homeostasis of gut microbiota are critical for host metabolism, immunity, and neurodevelopment (13, 14). In healthy individuals, Firmicutes and Bacteroidetes phyla dominate the gut microbiota (>90% combined abundance). In contrast, ASD patients exhibit significant dysbiosis characterized by reduced *α*-diversity, increased abundance of *Bacteroides* and *Clostridioides*, and marked depletion of *Prevotella,*
*Bifidobacterium*, and *Veillonella*. These alterations are closely associated with intestinal barrier disruption (“leaky gut”), systemic inflammation, and metabolic abnormalities (15, 16). Studies have revealed decreased levels of short-chain fatty acids (SCFAs) and elevated neurotoxic metabolites (e.g., isopropanol, p-cresol) in the feces of ASD children. Such imbalances may disrupt neurotransmitter equilibrium (e.g., serotonin, γ-aminobutyric acid) by crossing the blood-brain barrier, contributing to neuropsychiatric symptoms (17). Animal experiments further validate the causal role of gut microbiota: fecal transplants from ASD children into germ-free mice induce social deficits and repetitive behaviors, demonstrating microbiota-mediated modulation of the tryptophan-serotonin metabolic axis and central nervous function (18).

The gut microbiota interacts bidirectionally with the central nervous system through four pathways—neural, immune, endocrine, and metabolic—collectively forming the MGBA. Below are the potential mechanisms by which gut microbiota influences ASD-like behaviors via these pathways:
**Neural Pathway:** Gut microbiota produce short-chain fatty acids (SCFAs), such as butyrate, which activate vagal signaling and modulate neurotransmitters like glutamate and GABA, thereby affecting synaptic plasticity and neural transmission (19). Studies indicate reduced butyrate levels and aberrant glutamate metabolism in the gut microbiota of ASD children, correlating with impaired neurotransmission (19).Specific microbiota (e.g., *Lactobacillus*, *Bifidobacterium*) synthesize neuroactive compounds (e.g., GABA, serotonin precursors), directly or indirectly modulating the excitatory-inhibitory balance in the central nervous system. Notably, fecal GABA levels are reduced in ASD children, and probiotic supplementation has been shown to restore neurotransmitter metabolism (20).**Immune Pathway:** Dysbiosis (e.g., increased Proteobacteria abundance) disrupts intestinal barrier integrity, leading to “leaky gut,” which allows pro-inflammatory molecules like lipopolysaccharides (LPS) to enter systemic circulation. This triggers systemic inflammation, and cytokines (e.g., IL-6, TNF-α) exacerbate neuroinflammation by crossing the blood-brain barrier, worsening ASD symptoms (21). Gut microbiota also regulate immune homeostasis by balancing Th17/Treg cell activity. Enhanced Th17 pro-inflammatory responses in ASD children may drive central neuroinflammation, with specific taxa (e.g., Clostridioides) linked to Th17 pathway activation (22).**Endocrine Pathway:** Approximately 90% of serotonin (5-HT) is synthesized by enterochromaffin cells in the gut, relying on microbiota-dependent tryptophan metabolism. In ASD, aberrant tryptophan metabolism (e.g., enhanced kynurenine pathway) reduces serotonin synthesis, contributing to central serotonin deficiency, which impairs emotional regulation and social behavior (23). ASD children exhibit elevated colonic tryptophan hydroxylase (TPH1) expression, reduced serotonin transporter (SERT) levels, and prefrontal cortex TPH2 dysfunction (23). Additionally, gut microbiota modulates hypothalamic-pituitary-adrenal (HPA) axis activity via glucocorticoid regulation. Dysbiosis may amplify stress responses, aggravating ASD symptoms. Probiotic interventions have been shown to lower cortisol levels and alleviate anxiety in ASD children (24).**Metabolic Pathway:** SCFAs (e.g., butyrate, propionate), produced by microbial fermentation of dietary fiber, exhibit anti-inflammatory properties, maintain gut barrier function, and regulate gene expression. Reduced butyrate levels in ASD children may exacerbate intestinal permeability and neuroinflammation (25). Studies report significantly lower fecal butyrate in ASD patients compared to controls, with symptom improvement correlating with restored SCFA levels post-intervention (25). Gut microbiota also influence neural excitability via glutamate and GABA metabolism. Dysregulated glutamate pathways (e.g., decreased 2-ketoglutarate) in ASD may disrupt prefrontal cortex function. Probiotic interventions can normalize glutamate-related metabolites, suggesting therapeutic potential (19).In recent years, FMT has emerged as a promising alternative therapy for GI disorders. FMT involves transplanting functional microbiota from healthy donors into patients' GI tracts, restoring microbial composition and metabolism to alleviate dysbiosis and clinical symptoms (26). While FMT is guideline-recommended for recurrent *Clostridioides difficile* infection, it has also shown potential in neuropsychiatric disorders such as Parkinson's disease, depression, and ASD (27). However, it is important to acknowledge that there is a paucity of data on the use of FMT in children for indications beyond C. difficile infection, an area that requires further rigorous investigation (28). Unlike single-strain probiotics, FMT enables multidimensional modulation by transferring hundreds of microbial species, viruses, and fungi, offering comprehensive restoration of gut microbiota (26). A study demonstrated that FMT reduced Childhood Autism Rating Scale (CARS) scores by 22% and GI Symptom Rating Scale (GSRS) scores by 82%, with sustained increases in microbiota diversity and *Bifidobacterium/Prevotella* abundance for up to 8 weeks post-treatment (29).

However, FMT's clinical application remains contentious:
**Inconsistent Efficacy:** A randomized controlled trial (RCT) found no significant difference between oral FMT capsules and placebo, potentially due to donor variability or administration routes (30).**Safety Concerns:** Although most adverse effects (AEs) are mild to moderate, risks such as infections and long-term safety in ASD patients require further evaluation (31, 32).**Unclear Mechanisms:** While FMT alters gut microbiota composition in ASD, the pathways linking microbial changes to symptom improvement (e.g., specific metabolites or immune pathways) remain undefined, hindering biomarker-guided personalized therapy (33).**Uncertain Long-term Outcomes:** Long-term follow-up studies report diminishing therapeutic effects over time, with partial relapse of core symptoms in some patients (31).The complexity of ASD demands interdisciplinary collaboration. As a powerful tool to modulate the MGBA, FMT holds promise for addressing neurodevelopmental deficits at their root. Despite current limitations, advancements in mechanistic understanding, technological innovation, and clinical standardization may position FMT as a cornerstone of precision medicine for ASD, offering new hope for affected children and families. Future efforts must balance scientific rigor with clinical translation to bridge the gap between laboratory research and real-world therapeutic applications. Therefore, we hypothesize that multi-course FMT will significantly improve both GI symptoms and core behavioral deficits in children with moderate-to-severe ASD, and that these clinical improvements will be associated with the restoration of gut microbial diversity and function.

## Methods and analysis

2

### Study objectives

2.1

#### Primary objective

2.1.1

To investigate the clinical efficacy and safety of FMT in children with ASD.

#### Secondary objectives

2.1.2

2.1.2.1 To analyze changes in gut microbiota composition during FMT treatment in children with ASD.

2.1.2.2 To explore correlations between core microbiota and clinical outcomes.

### Study design

2.2

This is a prospective, open-label, single-arm, single-center clinical study enrolling children aged 2–12 years with moderate-to-severe ASD. The study aims to evaluate the efficacy and safety of FMT in ASD, investigate microbial colonization patterns, and identify core microbiota post-FMT. Findings will provide evidence-based support for clinical protocols and theoretical foundations for individualized precision therapy in ASD. A technical route map for the study is shown in Figure 1. All clinical data will be recorded on standardized Case Report Forms (CRFs) and entered into a secure, password-protected electronic database to ensure data quality and integrity.

**Figure 1 F1:**
[figure not shown]
Technical route map. BSFS, bristol stool form scale; ASD, autism spectrum disorder; FMT, fecal microbiota transplantation.

### Study participants

2.3

#### Inclusion criteria

2.3.1

Participants must meet all of the following criteria:
Aged 2–12 years.Diagnosed with ASD according to the Diagnostic and Statistical Manual of Mental Disorders, Fifth Edition (DSM-5), with a CARS total score ≥36 (moderate-to-severe autism).DSM-5 Diagnostic Criteria for ASD:
Onset in early developmental stages.Persistent deficits in social communication and interaction across multiple contexts, accompanied by restricted, repetitive patterns of behavior, interests, or activities.Symptoms cause clinically significant impairment in social, occupational, or other critical functional areas.Symptoms are not better explained by intellectual disability or global developmental delay.CARS Scoring System:
Total score <30: non-autistic.Total score 30–36: mild-to-moderate autism.Total score ≥36: moderate-to-severe autism.Legal guardians fully comprehend the trial's informed consent and voluntarily provide written consent.Compliance with follow-up visits, examinations, and specimen collection.No probiotic supplements consumed within the preceding 3 months.Participants on stable doses of psychopharmacological medications for at least 3 months prior to enrollment are eligible. No new psychopharmacological therapies may be initiated, and no dose changes are permitted during the study period.

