#### Exclusion criteria

2.3.2

Participants will be excluded if any of the following criteria apply:
Use of probiotics or prebiotics within 3 months prior to enrollment.Antibiotic usage within 1 month prior to enrollment.Presence of fever (axillary temperature ≥37.5 °C).Dependency on tube feeding.Severe GI conditions requiring immediate intervention (e.g., life-threatening intestinal obstruction, perforation, hemorrhage, ulcerative colitis, Crohn's disease, celiac disease, or eosinophilic esophagitis).Diagnosis of severe malnutrition, underweight status (BMI-for-age <3rd percentile), or severe immunodeficiency disorders.History of severe allergic reactions (e.g., anaphylaxis).Monogenic disorders (e.g., Fragile X syndrome, Rett syndrome).Comorbid psychiatric diagnoses, including depression, developmental speech/language disorders, intellectual disability, attention-deficit/hyperactivity disorder (ADHD), selective mutism, reactive attachment disorder, or childhood schizophrenia.

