#### Control of confounding variables

2.4.5

To minimize known confounding factors that can influence the gut microbiota, legal guardians will be instructed to maintain the child's typical diet and to avoid introducing major dietary changes (e.g., starting a gluten-free/casein-free diet) during the study period. A baseline 3-day dietary log will be collected. All concomitant medications and the use of supplements will be recorded at each study visit. While household environment cannot be controlled, data on significant dietary patterns and concomitant medications will be collected and considered as potential covariates in exploratory statistical models.

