#### Primary outcomes

2.5.1

1. **GSRS.**
a.**Timeframe**: Pre-FMT, during FMT, and at 1, 2, 3, 4, 5, 6 weeks, 3 months, 6 months,9 months and 12months post-FMT.b.**Description**: A 15-item questionnaire evaluating GI symptom severity. Each item is scored from 1 (“none”) to 7 (“very severe”), with descriptors: 1 (none), 2 (mild), 3 (slight), 4 (moderate), 5 (marked), 6 (severe), 7 (very severe). Participants with <50% reduction in mean GSRS scores are classified as non-responders.**2. CARS**
a.**Timeframe**: Pre-FMT, 3 months, 6 months,9 months and 12 months post-FMT.b.**Description**: Administered by trained assessors, this 15-item scale yields a total score ranging from 15 to 60. Scores are interpreted as: <30 (non-autistic), 30–36 (mild-to-moderate autism), and ≥36 (moderate-to-severe autism).

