#### Secondary outcomes

2.5.2

1.Daily Stool Record (DSR)
a.**Timeframe**: Pre-FMT, during FMT, and at 1, 2, 3, 4, 5, 6 weeks, 3 months, 6 months, 9 months and 12 months post-FMT.b.**Description**: Daily documentation of stool characteristics using the Bristol Stool Scale. The percentage of days with abnormal bowel movements (e.g., abnormal consistency, absence of stool, or use of GI medications) is calculated, with higher percentages indicating worse symptoms.2.Social Responsiveness Scale (SRS)
a.**Timeframe**: Pre-FMT, 3 months, 6 months,9 months and 12 months post-FMT.b.**Description**: A 65-item questionnaire assessing social skills. Items are scored 0 (“never true”) to 3 (“almost always true”), with total scores ranging from 0 to 195. Higher scores indicate greater social impairment.3.Aberrant Behavior Checklist (ABC)
a.**Timeframe**: Pre-FMT, 3 months, 6 months,9 months and 12 months post-FMT.b.**Description**: A 58-item checklist evaluating maladaptive behaviors. Total scores range from 0 to 174, with ≥31 indicating autism tendency and >53 confirming an autism diagnosis. Higher scores reflect more severe behavioral issues.4.Microbiota Analysis
a.**Sequencing Method:** Fecal samples will be subjected to metagenomic next-generation sequencing (mNGS) to comprehensively characterize the gut microbiota at both taxonomic and functional levels. Total microbial DNA will be extracted from fecal samples, followed by library construction and shotgun sequencing on an Illumina NovaSeq platform (or equivalent), aiming for a sequencing depth of at least 10 Gbp per sample to ensure adequate coverage for both abundant and rare species, as well as functional gene analysis.b.Bioinformatic and Statistical Analysis Pipeline:

The raw sequencing data and subsequent analyses will adhere to the following rigorous bioinformatics procedure to ensure accuracy and reproducibility.

Step 1: Raw Data Quality Control.

To assess sequencing quality and detect potential contamination, FastQC (Version 0.12.1) (36) and MultiQC (Version 1.15) (37) will be utilized with default parameters. Key quality metrics include ≥80% of bases with a Q-score >30, adapter content <5%, and GC distribution within the expected range of 40%–50%. The output report, ASD_FMT_Raw_QC.html, will be reviewed to exclude samples that fail to meet these criteria.

Step 2: Read Trimming and Host DNA Removal.

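### No pre-entry stability is required for GI medication or restrictive diet although GSRS is a primary outcome, and later GI medication has no consistent handling in the GSRS analysis

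*Protocol article*

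**What the plan says.** **Entry.** Section 2.3.1 states "Participants on stable doses of psychopharmacological medications for at least 3 months prior to enrollment are eligible" and continues: "No new psychopharmacological therapies may be initiated, and no dose changes are permitted during the study period". It also asks for 3 months without probiotic supplements. Section 2.3.2 excludes "Use of probiotics or prebiotics within 3 months prior to enrollment" and antibiotics within 1 month. Neither list mentions laxatives, antidiarrhoeals, other GI drugs or the length of time a diet has been in place.

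**During the study.** Section 2.4.5 tells guardians to "maintain the child's typical diet and to avoid introducing major dietary changes (e.g., starting a gluten-free/casein-free diet) during the study period". On diet it adds "A baseline 3-day dietary log will be collected". Concomitant medication and supplements are recorded at every visit and may enter exploratory models as covariates. Section 2.3.4 eliminates from the final analysis participants with unapproved concomitant therapies, or with medications or interventions during the study that could confound the results.

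**Outcomes.** GSRS is one of two primary outcomes (2.5.1): "Participants with <50% reduction in mean GSRS scores are classified as non-responders". Nothing there refers to GI medication. The Daily Stool Record, a secondary outcome (2.5.2), counts a day as abnormal for reasons such as "abnormal consistency, absence of stool, or use of GI medications".

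**Analysis.** Section 2.7.1 defines the per-protocol population as those who complete the 12-month assessment, and the ITT population as those enrolled who received at least one FMT. Neither definition refers to section 2.3.4.

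**The concern.** The trial has no control arm, so every change in GSRS after baseline is attributed to FMT. The protocol sees this risk for behavioural outcomes and requires 3 months of unchanged psychopharmacological treatment. For the GI outcome it removes some influences on the gut (probiotics, prebiotics, antibiotics) but not the treatments aimed most directly at the symptoms GSRS measures. A child who began a laxative or a restrictive diet shortly before the baseline score can enter, keep it as the usual regimen, and go on improving from it during follow-up.

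At stake is the direction of error in a primary outcome. Such improvement pushes towards apparent benefit, and the covariate models that might reveal it are exploratory only. After entry there is a second problem: different sections imply different treatment of a child who starts GI medication, so the GSRS result depends on which section the analyst follows.

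**Working it through.** **1. The plan's own figures.** The only quantitative basis in the protocol is the CARS sample size (2.8), and it reproduces:
- SD of the difference = √(6.5² + 6.7² − 2 × 0.5 × 6.5 × 6.7) = √43.59 = 6.60.
- n = (1.96 + 0.8416)² × 43.59 / 4.2² = 19.4, rounded up to 20.
- With 20% dropout, 20 / 0.80 = 25; 30 are planned.

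This concerns CARS only. The protocol gives no SD for GSRS and no rate of GI co-medication.

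**2. Treatment begun before the baseline score.**
- Sections 2.3.1 and 2.3.2 contain no rule on GI medication or duration of diet.
- The instruction in 2.4.5 preserves whatever diet is typical at entry. With no prior stability period, a recent diet can qualify.
- Section 2.3.4 concerns what is given during the study.
- Table 1 places baseline GSRS within 1 month before FMT. Benefit already achieved by then is in the baseline score; only benefit accruing afterwards is misattributed.

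The gap is therefore open, but limited to that remaining benefit.

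**3. GI medication begun or increased after entry.**

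| Section | What happens to the child |
|---|---|
| 2.3.4 | Eliminated, if the medication is judged able to confound; no GI drug is named |
| 2.4.5 | Retained; medication recorded, possible covariate in exploratory models |
| 2.5.1 GSRS | Scored as usual; medication ignored |
| 2.5.2 Daily Stool Record | Retained; days with GI medication count as abnormal |
| 2.7.1 | In ITT after one FMT; in per-protocol if 12 months are completed |

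These cannot all govern the same child.

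**4. Direction under each reading.** If the child is retained and scored as usual, improvement from the drug counts towards FMT. If the child is eliminated, r responders out of 30 become r out of 30 − k when the k children removed were non-responders. Suppose, as an assumption, that 10% to 30% of children start GI treatment (k = 3 to 9) and none had responded. The responder rate is then multiplied by 30/27 = 1.11 to 30/21 = 1.43. Either reading can favour FMT.

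**5. Illustration for the mean change.** Assumptions, none from the protocol: FMT has no effect on GSRS; 10% to 30% of children have a co-intervention whose benefit accrues after baseline; that benefit is 0.5 to 1.0 SD of the GSRS change; the SD itself is unaffected.
- Mean shift d: 0.10 × 0.5 = 0.05 SD to 0.30 × 1.0 = 0.30 SD.
- Rejection probability of a two-sided 5% paired t-test, from the noncentral t distribution with n − 1 degrees of freedom and noncentrality d√n:
  - n = 30 (noncentrality 0.27 to 1.64): about 6% to 36%.
  - n = 24, that is 30 × 0.80 (noncentrality 0.24 to 1.47): about 6% to 29%.

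The nominal rate is 5%. The range shows how strongly the answer depends on the assumed rates; it is not an estimate for this trial.

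**The case against.** The strongest counter-argument is that the protocol does control GI co-interventions. It removes probiotics, prebiotics and antibiotics before entry, asks families not to change the diet, records all medication, and eliminates participants given confounding treatment. Baseline GSRS already absorbs most of what an earlier laxative achieved. GSRS and the stool record are different instruments and need not agree. Handling of new medication is a matter for an analysis plan, which is not shown.

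Much of this stands, and it rules out three stronger readings.
- A reader might infer that any laxative or diet started after entry simply counts as FMT benefit. The protocol does not support that: 2.4.5 discourages major diet changes and 2.3.4 can remove children given confounding treatment.
- A reader might infer that the two GI outcomes contradict each other. They do not; they differ in how they treat GI medication, and the protocol gives no reason.
- A reader might put a figure on false responders: if 10% to 30% start treatment and half respond because of it, 30 × 0.10 × 0.5 = 1.5 to 30 × 0.30 × 0.5 = 4.5 children, or 5 to 15 percentage points. Those rates are assumptions, they pool starts before and after entry, and section 2.7.1 states no test of a responder rate. The figure should not be cited as a finding.

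The objection does not reach the entry criteria. They are set out in the article as conditions that must all be met, and they are not left to an analysis plan. Nor does it remove the conflict between 2.3.4 and 2.7.1, both of which are stated in the article.

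**Conclusion.** The concern holds in a limited form. No stable period for GI medication or restrictive diet is required before entry, and in this uncontrolled design benefit still accruing after the baseline score would be attributed to FMT. After entry, safeguards exist, but they name no GI medication, rely on judgement in an open-label trial, and are not carried into the analysis populations. Elimination would itself favour FMT if the children who need new GI treatment are those FMT did not help, which is plausible but not shown by the protocol.

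The size cannot be computed from the protocol; the ranges in the working rest on stated assumptions. The point deserves correction because it affects a primary outcome, the likely direction is towards success, and the correction is cheap. It does not affect the CARS sample size.

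**What to change.** 1. In 2.3.1, add a pre-entry stability requirement for regular GI medication and restrictive diet, parallel to the existing 3-month psychopharmacological criterion. Which treatments it covers, and for how long, is for the investigators to set.
2. Reconcile 2.3.4, 2.4.5, 2.5.2 and 2.7.1 so that children who start or increase GI medication stay in the analysis, and state this in the population definitions. This concerns the analysis only and need not restrict care.
3. In 2.5.1 and 2.7.1, report GSRS change and responder rate with and without visits at which GI medication was newly started or increased since baseline. Include an analysis that counts those visits as non-response, in line with the logic of the stool record.

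No new visits are needed: concomitant medication is already recorded at each visit and GI medication use already enters the stool record. The cost is protocol wording, a few deferred enrolments and possibly a lower reported responder rate.
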